**Methods and analysis:**

The Acute Care QUAliTy in chronic Kidney disease (ACQUATIK) study is a prospective, observational, multicentre cohort study. Over 4000 patients will be recruited with an enrolment period of 2 years and a follow-up period of 2–4 years. Patients under follow-up by a renal team will be excluded. Data will be obtained from patient and hospital records during the index admission. Preadmission data will be extracted from general practice records based on the Quality and Outcomes Framework. Diagnosis, comorbidities and procedure data pertaining to the index and subsequent admissions will be extracted from the Hospital Episode Statistics database and long-term mortality data will be tracked using the Office of National Statistics. This information will allow us to examine a complete patient journey through primary and secondary care, providing unequalled levels of information on treatment and outcomes of patients with CKD. The combined data set will be used to compare outcomes and treatments among patients with CKD versus patients without CKD. The primary end point is hospital readmission rates. The relationship between age, sex, ethnicity, socioeconomic status and concurrent comorbidities will be analysed to determine their influence on outcomes and treatments.

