## Introduction

### Chronic kidney disease

Current definitions of chronic kidney disease (CKD) use surrogates of kidney damage (comprising at least one of: proteinuria, abnormal urinary sediment, histological or structural abnormality or history of a renal transplant) and/or a glomerular filtration rate less than 60 mL/min/1.73 m^2^ present on at least two occasions for 3 months or more.^1^
^2^ The prevalence of early CKD is increasing and now affects more than 13% of the population in the developed world.^3^ This increase has been largely driven by the increasing prevalence of the most common risk factors for CKD, including diabetes, hypertension and older age.^3^ Among adults aged more than 70 years, the prevalence of CKD has been estimated to be more than 40% in the USA and UK.^3^ For an important minority, CKD can progress to end-stage renal disease (ESRD) requiring renal replacement therapy (RRT) in the form of either dialysis treatment or kidney transplantation.^1^ The cost of CKD to the National Health Service (NHS) in England in 2009–2010 has been estimated at £1.45 billion^4^; indirect costs may be far higher.^5^ The shift in focus to active early detection and management of CKD, and other chronic conditions, has become an increasing priority for health services. Indeed, most patients with CKD are now managed in the primary care setting with little or no secondary care input.^6^ However, US data demonstrates that patients with CKD are more likely to be readmitted after a hospital admission than patients without CKD,^7^ with the associated increase in costs and comorbidity.

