### Secondary outcomes

Hospital readmission rates for any cardiovascular event (including acute myocardial infarction, angina, coronary artery bypass graft surgery, percutaneous coronary intervention, peripheral arterial disease, revascularisation or stroke) in patients with and without CKD.All-cause and cardiovascular mortality in patients with and without CKD.Treatment received before, during and after admission to hospital with a cardiovascular event by patients with and without CKD.The risk: benefit ratio for primary and secondary prevention of cardiovascular disease in patients with and without CKD.Attainment of standards in chronic disease management in patients with and without CKD.Rates, severity and risk factors for acute kidney injury in patients with and without CKD.The proportion of patients with biochemical evidence of CKD not classified so by the GP.All primary and secondary outcomes will be analysed separately to investigate the influence of age, sex, ethnicity, socioeconomic status, deprivation score and concurrent comorbidities (including diabetes mellitus) on outcomes, treatment and classifications. Determination of socioeconomic status will be based on the Index of Multiple Deprivation model calculated at the local level.^34^

In the ACQUATIK study patients with renal disease under secondary care nephrology follow-up have been excluded. Therefore, the majority of diagnoses coded within HES and primary care databases will include common systemic conditions such as hypertension and diabetes mellitus as the aetiology of CKD, rather than primary renal glomerulonephritides which would invariably be under secondary care follow-up in the UK. Conditions such as diabetes mellitus will also be present in the non-CKD group and will form part of the prespecified analysis of comorbidities during data analysis.

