## Analyses

Normally distributed continuous data will be presented as mean±SD with comparisons made using Student's t test or one-way analysis of variance. Non-normally distributed data will be presented as median (IQR) and analysed using the Kruskal-Wallis test. Categorical data will be presented as count (percentage) and analysed using the χ^2^ test. In multivariable analyses, variables found to be significantly associated with the outcome under investigation in the univariable analyses will be used. Logistic regression analysis will be used to assess the relationship between outcomes and parameters under investigation and the results expressed as an OR with 95% CIs. Time-to-event data analysis will be performed using the Cox proportional hazards model and the results expressed as HR with 95% CIs.

Standard methods will be used to handle missing data after being assessed for extent and as to whether this is due to random missingness and/or censoring.^37^
^38^

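### One significance-based rule for all multivariable models does not separate confounders from intermediates, so the planned adjusted coefficients for ethnicity and deprivation need not equal their total influence

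*Protocol article*

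**What the plan says.** The abstract of the protocol article states the aim: "The relationship between age, sex, ethnicity, socioeconomic status and concurrent comorbidities will be analysed to determine their influence on outcomes and treatments". The Secondary outcomes section extends it to all primary and secondary outcomes, which are to be "analysed separately to investigate the influence of age, sex, ethnicity, socioeconomic status, deprivation score and concurrent comorbidities". Ethnicity, deprivation and comorbidity thus stand in one list, with no ordering among them. The same section adds that conditions such as diabetes "will form part of the prespecified analysis of comorbidities during data analysis".

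The Analyses section gives a single rule for choosing covariates: "In multivariable analyses, variables found to be significantly associated with the outcome under investigation in the univariable analyses will be used". The models named are logistic regression ("Logistic regression analysis will be used to assess the relationship between outcomes and parameters under investigation") and, for event times, Cox regression ("Time-to-event data analysis will be performed using the Cox proportional hazards model"). Nothing in the article varies the covariate set with the factor being studied or keeps comorbidities out of any model.

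**The concern.** The right covariates depend on which factor's influence is wanted. Diabetes may confound the comparison of patients with and without CKD. It cannot cause a patient's ethnicity, and it may well follow from deprivation. A screen on association with the outcome cannot tell these roles apart, because a confounder and an intermediate both predict the outcome.

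If a comorbidity lies between deprivation and readmission, adjusting for it removes the part of the association that passes through it. What is left answers a narrower question than the one in the abstract. A gradient across social or ethnic groups could look smaller or larger than it is, or be reported as absent, on a question that the study names as its own. This differs from the familiar complaint that p-value screening can drop confounders: the fault would remain even if every confounder were kept.

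**Working it through.** **The plan's own figures.** The article gives no figure for ethnicity or deprivation. Its only computable figures are the power values for the CKD comparison. I used a two-sample Poisson rate test with a 60:40 split, 2 years per patient and two-sided 5% (assumed; not stated). This gives 91.9% against the stated 92% (N=2000, 82 v 116 per 1000 patient-years) and 79.6% against 80% (N=4000, 56 v 72), with pooled variance under the null. They reproduce. They also bear on the screen: if CKD is screened at 5% on this comparison, it enters the models with about 80% probability at N=4000 even in the worst case.

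**Total against adjusted influence.** Take one binary comorbidity with prevalence m0 in the unexposed and m1 in the exposed group, rate ratio RRm for the outcome, and RRd for exposure with comorbidity held fixed:

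RR_total = RRd × [1 + m1(RRm − 1)] / [1 + m0(RRm − 1)]

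The comorbidity-adjusted model estimates RRd. All inputs in the table are assumed, with RRm = 1.5.

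| Case | m0, m1 | RRd (adjusted) | RR_total | Effect of adjusting |
|---|---|---|---|---|
| A | 20%, 40% | 1.10 | 1.10 × 1.20/1.10 = 1.20 | towards 1 |
| B | 40%, 20% | 1.10 | 1.10 × 1.10/1.20 = 1.01 | away from 1 |
| C | 20%, 40% | 0.80 | 0.80 × 1.20/1.10 = 0.87 | away from 1 |

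A Poisson simulation of 400,000 patients (30% exposed) agrees. Age-adjusted and then age-and-comorbidity-adjusted rate ratios were 1.19 and 1.09 (A), 1.00 and 1.09 (B), and 0.87 and 0.80 (C).

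**Range.** For RRm, the article's CKD rate ratios are 72/56 = 1.29 and 116/82 = 1.41; 2.0 is an assumed upper value. The ratio RR_total/RRd is then:
- m0 = 20%, m1 = 30% to 40%: from 1.087/1.058 = 1.03 to 1.40/1.20 = 1.17.
- m0 = 30% to 40%, m1 = 20%: from 1.20/1.40 = 0.86 to 1.058/1.087 = 0.97.

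**Can the univariable result stand in?** No, because it is confounded by age. Take case A with the exposed group 8 years younger and a log-rate rise of 0.04 per year of age (both assumed). The crude ratio is about 1.20 × exp(−0.32) = 0.87; the simulation gave 0.86, against 1.19 after age adjustment. The crude estimate points the wrong way.

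**The case against.** **The article does not say that influence will be read only from a mutually adjusted model.** True. Univariable analyses are planned too, and separate analysis by factor could mean stratified analyses. A reader might infer that the fully adjusted coefficient will be reported as the influence, but that is an inference. What stands is that separate analysis names no adjustment set, the crude result is confounded by age, and the screened model is the only adjusted analysis described.

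**Direction.** A reader might infer that the influence of ethnicity and deprivation is bound to be understated. The documents do not support that: cases B and C go the other way. Conditioning on a comorbidity that shares unmeasured causes with the outcome can also bias the coefficient in either direction.

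**The pathway is not in the documents.** The Introduction links diabetes, hypertension and older age to CKD and does not bring ethnicity or deprivation into that statement. Long illness can also lower socioeconomic status, so comorbidity may partly confound deprivation. This is why the comorbidity-adjusted model should be kept beside the other one.

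**Treatment received.** Whether patients with the same clinical need are treated differently is a legitimate question, and it requires comorbidity adjustment. The criticism is weak there.

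**Power.** It is tempting to express the point as lost power. That would compare tests of two different quantities and rest on invented effect sizes.

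**Detail left to a fuller document, and no causal claim.** Adjustment sets can be left to an analysis plan, but here the article states a rule, and the rule does not fit the aim. The article does disclaim causality, and prespecified sets would also answer a general objection to p-value screening. Neither point makes the rule fit the aim.

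**Conclusion.** The point holds in a limited form. The rule in the Analyses section makes the only planned adjusted coefficients for ethnicity and deprivation conditional on any comorbidity that passes the screen. They need not equal the total influence that the abstract and the Secondary outcomes section ask for.

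The difference can go either way. It is most plausibly towards no effect where the comorbidity is commoner in the disadvantaged group and harmful. Its size cannot be computed from the documents; the illustrative factor of 0.86 to 1.17 between total and adjusted rate ratio rests on assumed prevalences and on one comorbidity.

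The conclusion assumes that at least one comorbidity passing the screen lies partly downstream of ethnicity or deprivation. The primary comparison of readmission with and without CKD is not affected by this point.

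**What to change.** In the Analyses section, replace the univariable screen with a prespecified adjustment set for each factor listed under Secondary outcomes:

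- **Ethnicity:** the main model adjusts for age and sex. Deprivation is left out because it may itself follow from ethnicity.
- **Deprivation:** the main model adjusts for age, sex and ethnicity.
- **Second model for each:** add comorbidities and CKD, and label the result as the association not explained by comorbidity.
- **Treatment received:** report both models side by side, since the comorbidity-adjusted one answers the question of equity given clinical need.

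The cost is one more model per outcome, a few lines of text and a longer results table. No new data are needed.

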## Methods and analysis

### Study design

The ACQUATIK study is a prospective, multicentre observational study of patients in the UK with and without CKD. Two main centres in Birmingham, University Hospitals Birmingham NHS Foundation Trust (UHBFT) and Heart of England NHS Foundation Trust (HEFT) are undertaking this study. Each centre has a high number of admissions and serves a large diverse population.

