### Hospital Episode Statistics

Hospital Episodes Statistics (HES) is an administrative data set that collates information on all patients admitted to all NHS hospitals in England. Each admission contains a primary diagnosis and up to 19 secondary diagnoses (recorded using the standard system of International Classification of Diseases, 10th edition), and up to 24 procedure fields. In addition to diagnostic and procedural codes, the HES database^31^ also records the Charlson comorbidity index. Derived from the secondary diagnoses codes, this is a marker of comorbidity and was originally formulated to predict mortality.^32^ The Carstairs index of deprivation is derived from the patient's postcode.^33^ As well as clinical information, each HES record will also contain routine information about the patient (eg, age, sex, ethnicity and postcode) and the episode of care (eg, hospital name, emergency admission, date of admission and discharge). All hospitals in England are required to submit data to HES.

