## Outcome measures

### Primary outcome

Hospital readmission rates in patients with and without CKD.

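### Choosing adjustment covariates by univariable significance suits the non-randomised CKD comparison poorly: weak or masked confounders can drop out, and a pre-specified set would avoid this (should-fix)

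*Protocol article*

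**What the plan says.** The study is a "prospective, multicentre observational study of patients in the UK with and without CKD", and the abstract says the linked data will be used to "compare outcomes and treatments among patients with CKD versus patients without CKD". The primary outcome is "Hospital readmission rates in patients with and without CKD".

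For multivariable models, the Analyses section says that "variables found to be significantly associated with the outcome under investigation in the univariable analyses will be used". Results are then given as "results expressed as an OR with 95% CIs" for logistic regression, or from a "Cox proportional hazards model and the results expressed as HR with 95% CIs". No covariate is named as always included.

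The Secondary outcomes section says that each outcome will also be examined for the "influence of age, sex, ethnicity, socioeconomic status, deprivation score and concurrent comorbidities (including diabetes mellitus) on outcomes, treatment and classifications". It treats these as factors whose own influence is of interest. It does not say that the CKD contrast is always adjusted for them. The same section refers to a pre-specified analysis of comorbidities, again without making it an adjustment set.

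**The concern.** A variable confounds the CKD comparison through its links with both CKD and the outcome. The stated rule tests only the second link, one variable at a time, by p-value. Three things follow.

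- A weak confounder is kept or dropped largely by chance. Several dropped together can add up to a visible bias.
- A confounder that is more common in CKD but acts against it can look unrelated to the outcome in a univariable test. It is then dropped systematically.
- Readmission, cardiovascular readmission and mortality can each end up with a different adjustment set, so the CKD estimates are not comparable across outcomes.

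This is not a detail left to an analysis plan. The article states a rule, and an analysis plan that followed it would inherit the weakness.

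**Working it through.** **1. The plan's own figures.** The rates under Number of patients set the scale: 116 vs 82 and 72 vs 56 per 1000 patient-years, 40% with CKD, 2 years' average follow-up. Two-sided alpha of 0.05 is assumed. Power = Φ[(d − 1.96·SE0)/SE1], where SE0 uses the pooled rate and SE1 the separate rates.

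- N = 2000: SE0 = √[0.0956(1/1600 + 1/2400)] = 0.00998; SE1 = √(0.116/1600 + 0.082/2400) = 0.01033; power = Φ[(0.034 − 0.01956)/0.01033] = 91.9% (stated 92%).
- N = 4000: SE0 = √[0.0624(1/3200 + 1/4800)] = 0.00570; SE1 = √(0.072/3200 + 0.056/4800) = 0.00585; power = Φ[(0.016 − 0.01117)/0.00585] = 79.6% (stated 80%).

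The stated power reproduces, and this point disputes no figure. The lower-rate scenario gives 1600×2×0.072 + 2400×2×0.056 = 499 readmissions. That is ample for a fixed model of modest size, so parsimony is no reason to screen.

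**2. Simulation set-up.** Poisson readmission counts, 4000 patients, 40% with CKD. A covariate is kept only if its univariable |z| exceeds 1.96. The resulting CKD rate ratio (RR) is compared with that from a model forcing all confounders in. Confounder strengths and prevalences are assumptions; none comes from the documents.

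**3. Eight weak confounders** (prevalence 30% in CKD, 15% without; base rate 0.05 per year; follow-up uniform on 2 to 4 years).

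| True CKD RR | Confounder RR | Kept | CKD RR, screened | CKD RR, forced | Coverage, screened / forced |
|---|---|---|---|---|---|
| 1.00 | 1.10 | 25% | 1.05 | 1.00 | 90.0% / 93.5% |
| 1.00 | 1.15 | 53% | 1.04 | 1.00 | 92.7% / 95.2% |
| 1.00 | 1.20 | 80% | 1.02 | 1.00 | 94.5% / 94.9% |
| 1.286 | 1.10 | 53% | 1.306 | 1.291 | 96% / 96% |
| 1.286 | 1.15 | 82% | 1.296 | 1.289 | 96% / 96% |

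The harm shrinks when CKD has a real effect because part of that effect leaks into each confounder's univariable association. The CKD share is 0.12/0.21 = 0.571 among those with the confounder and 0.28/0.79 = 0.354 among those without. With 72/56 = 1.286, and ignoring the other seven, a true RR of 1.10 appears as 1.10 × (1 + 0.571×0.286)/(1 + 0.354×0.286) = 1.16, so it passes more often.

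**4. One masked confounder** (60% in CKD, 20% without, RR 1/1.20; true CKD RR 1.286; rate 56 per 1000 patient-years, 2 years). The CKD share is 0.24/0.36 = 0.667 with the factor and 0.16/0.64 = 0.25 without. Its univariable RR is (1/1.20) × (1 + 0.667×0.286)/(1 + 0.25×0.286) = 0.93 instead of 0.83. The screen keeps it in only 13% of runs. The CKD RR averages 1.22 screened against 1.29 forced, and power falls from 70% to 53%. At RR 1/1.12 it is kept in 5% of runs, with 1.23 against 1.28.

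**5. Strong confounders.** A confounder of RR 1.6 (60% vs 30%) is kept in every run, and the two models agree. An age-like confounder, RR 82/56 = 1.46 at 75% vs 40%, is kept in practically every run, again with no difference.

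**The case against.** The strongest reply is that the rule does little damage in this study. Strong confounders survive the screen at this sample size. At the rate ratio of 1.29 that the plan itself uses, eight weak confounders shift the estimate by 0.02 or less and cost no coverage. The visible bias needs either no CKD effect with many weak confounders all acting the same way, or a protective factor three times as common in CKD. The documents name no such factor, and the CKD drivers named in the Introduction (diabetes, hypertension, older age) would be expected to act the other way. The article also lists the relevant factors under Secondary outcomes, and its limitations say that causality cannot be attributed.

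Most of this stands, and it sets the grade. It does not rescue the rule. A list of factors whose influence will be studied is not a commitment to adjust the CKD comparison for them. An associational comparison still has to say what it is adjusted for. The size of any CKD effect in Birmingham is what the study sets out to learn, so the analysis should not be sound only when that effect is large. The screen also has less power for rarer secondary outcomes and would probably drop more there; that was not simulated.

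**Conclusion.** The selection rule is stated, fits a confounded comparison poorly, and is easily replaced. Its harm is confined to weak or masked confounders and probably rarer outcomes. Under the assumed strengths, the spurious RR is about 1.03 to 1.05 with coverage of 90 to 93% when there is no CKD effect and the eight confounders have RR 1.10 to 1.15. The bias is negligible at RR 1.29, and in the masked case 1.29 falls to about 1.22. Severity: should-fix.

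Three stronger readings are tempting, and the documents do not support them.

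- **That age would go uncontrolled.** If 75% of CKD and 40% of non-CKD patients were 66 or over (an assumption), the crude ratio would be (0.75×116 + 0.25×72)/(0.40×82 + 0.60×56) = 105.0/66.4 = 1.58. Standardised to 54% aged 66 or over it would be 95.8/70.0 = 1.37. That gap is the cost of not adjusting for age at all. The screen would keep age, so the rule does not cause it.
- **That the confidence intervals are invalid in their own right.** The article mentions no allowance for selection, but with the eight weak confounders the coverage loss came with omitted-confounder bias and went when that bias went.
- **That two deprivation scores would enter together.** "The Carstairs index of deprivation is derived from" the postcode, but only as a description of the hospital data. Socioeconomic status is assigned to the Index of Multiple Deprivation. Overlapping scores would mainly blur each other's coefficients, not bias the CKD estimate.

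**What to change.** Replace the selection sentence in the Analyses section with a fixed adjustment set, used for every CKD versus non-CKD comparison regardless of p-values: age, sex, ethnicity, Index of Multiple Deprivation, diabetes, hypertension and hospital. Report unadjusted and adjusted estimates side by side.

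Show further adjustment for cardiovascular comorbidities as an additional model, not as the main result. The Introduction links CKD to excess cardiovascular events, so these conditions may be consequences of CKD, and adjusting for them could remove part of the difference under study. Label any data-driven covariate selection as a sensitivity analysis.

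The variables come from sources the article already plans to use (questionnaire, general practice registers, hospital records). The cost is a paragraph of analysis wording, and the sample size does not change. It should be settled before outcome data are examined, since a set chosen afterwards is no longer pre-specified.
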